#### Laboratory quality assurance

The EPHI Food and Nutrition Laboratory will be responsible for the folate microbiological assay and the analyses of urinary iodine. For each of these analyses, the laboratory prepares pooled reference materials with low, medium and high concentrations. These pools are analysed 30 times and compared with appropriate external standards. The same pooled samples are analysed with each subsequent daily analytical run, and the results must fall with the range (±2 SD) of the original analyses for the day’s results to be considered acceptable. The laboratory will participate in the CDC Performance Verification Program for the Folate Microbiologic Assay. Under this external quality assurance (EQA) programme, CDC provides 10 samples per quarter in duplicate, and the participating laboratory returns results to CDC after each of the four challenges. CDC returns a brief summary report after each challenge and a comprehensive annual performance report showing the measurement imprecision and the per cent difference compared with the CDC Clinical Laboratory Improvement Amendments (CLIA)-approved folate microbiological assay. The laboratory also participates in the CDC EQA programme for urinary iodine procedures (Ensuring the Quality of Urinary Iodine Procedures).^51^

The EPHI Clinical Laboratory will complete analyses of serum vitamin B_12_, holotranscobalamin, homocysteine, thyroglobulin, glucose, and insulin and urinary sodium and potassium, all of which are completed on the COBAS 6000 analyser using special reagent kits and controls for each analyte. Each day, the COBAS analyser is standardised for each analyte to ensure conformity with acceptable result ranges, as specified by the manufacturer. This laboratory participates in the Oneworld Accuracy EQA programme.^52^ Under this programme, the laboratory analyses five unknown samples for each analyte every 4 months, and the results are compared for multiple consensus laboratories. The EPHI laboratory has been fully accredited for analyses of vitamin B_12_, glucose, and insulin and urinary sodium and potassium.

#### Assessment of SAEs

SAEs are defined as any illness or disorder that results in death or long-term disability, or requires an overnight stay in a clinical facility, regardless of the nature of the condition.^53^ All SAEs will be recorded during the biweekly home visits and reported within 48 hours to the co-PIs, who will classify them as being ‘likely to be related to the intervention’ or ‘unlikely to be related to the intervention’. The co-PIs will share these findings with the IRB on a monthly schedule.

We have established an external Data and Safety Monitoring Board (DSMB) to review whether any SAEs occur more frequently in any of the study groups. The DSMB comprises an Ethiopian physician, a statistician, a nutritionist, a staff member of the Ethiopian Food and Drug Authority and a person with expertise in research ethics. A list of all SAEs will be recorded continuously for periodic review by the DSMB statistician, who is not participating in the core study team. The DSMB statistician will aggregate the SAEs by study arm for review by the DSMB. The review frequency will depend on the number of new SAEs occurring over time. The DSMB will have the authority to interrupt or stop the trial if there is a significant excess number of SAEs that may be related to the intervention in either folic acid group.

### Sample size estimates

The sample size estimation is based on the number of women required to detect a clinically significant change in their RBC folate concentration in response to the intervention. According to the 2016 Ethiopian National Micronutrient Survey,^13^ the estimated mean RBC folate concentration among WRA is 507 nmol/L. If we assume a coefficient of variation of 35%, as has been observed in most other studies (as summarised in table 1),^2854^,^56^ the corresponding SD for Ethiopian women would be 177.5 nmol/L. To detect an effect size of 0.5 SD units (ie, 89 nmol/L), which would represent the difference in the change in mean RBC folate concentration from baseline to 6 months between women in the control group and women in the group receiving salt fortified with 200 μg folic acid per day, 85 participants per group are necessary. A difference of 89 nmol/L is equivalent to 18% of the expected mean RBC folate concentration at baseline, which is more conservative than the 27% change observed among women receiving a 100 µg folic acid supplement in a study by Hao *et al*.^28^ This calculation assumes an alpha of 0.05 and power of 0.90. After adjusting the sample size to account for the three-cell design, and an additional 15% to account for possible attrition, the total required sample size per group is 120 participants (ie, 360 participants total). This sample size will allow for comparisons between any two of the study arms.

**Table 1 T1:** Published data regarding population RBC folate concentration and responses to intervention trials

Study	Folic acid dose	n	Mean (or geometric mean)	SD (or CI)	Estimated SD	Coefficient of variation, CV (%)	% change from baseline	Ref
Ethiopia national survey	–	1121	511	(487, 527)	340	67.1	–	13
Guatemala national survey	–	1448	727	(711, 738)	262	36.0	–	54
Hao baseline	–	339	594	(572, 618)	216	36.3		28
Hao 6 months	100 μg/day	339	760	(731, 789)	272	35.6	27.9	28
Hao 6 months	400 μg/day	338	1036	(997, 1076)	370	35.8	74.4	28
Johansson baseline	166 μg/day		577	93		16.1	–	55
Johansson 3 months	166 μg/day		694	154		22.2	20.3	55
Johansson baseline	355 μg/day		784	238		30.3	–	55
Johansson 3 months	355 μg/day		987	167		16.9	25.9	55
Lamers baseline	–	34	668	(593, 752)	236	35.4	–	56
Lamers 24 weeks	400 μg/day	34	1290	(1200, 1370)	496	38.4	93.1	56

RBCred blood cell

Based on information on urinary iodine concentration among WRA published in the 2016 National Micronutrient Survey (median=96.7 µg/L, IQR 57.6–170.5),^13^ this sample size will permit detection of a 35 µg/L difference in urinary iodine concentration in either of the arms receiving folic acid-fortified salt compared with the control group (alpha=0.05; beta=0.90). Because we will obtain information on mean 24-hour urinary iodine concentration and total daily urinary iodine excretion rather than just single urine samples, we should be able to detect an even smaller effect size than would be possible with just a single sample.

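### The 35 µg/L detectable iodine difference spends all 120 women per arm, including those already set aside for attrition, and its power is labelled as beta

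*Protocol article*

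**What the plan says.** The Sample size estimates section of the protocol article sizes the trial on red-cell folate. For a 0.5 SD difference, "85 participants per group are necessary", and "This calculation assumes an alpha of 0.05 and power of 0.90". That number is then raised for the three-arm design and for "an additional 15% to account for possible attrition, the total required sample size per group is 120 participants".

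The next paragraph turns to urinary iodine. From a national survey ("median=96.7 µg/L, IQR 57.6–170.5") it concludes that 35 µg/L is detectable with the planned numbers, stated as a "difference in urinary iodine concentration in either of the arms receiving folic acid-fortified salt compared with the control group (alpha=0.05; beta=0.90". It gives no SD, evaluable number, attrition allowance or multiplicity adjustment for this statement. It adds, without a figure, that 24-hour collections should allow a smaller effect to be detected than single samples would.

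Elsewhere, the Study design section lists markers of iodine intake and status, including urinary iodine excretion, among the primary endpoints. The statistical analysis section plans analysis of covariance with the baseline value as covariate.

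**The concern.** There are three problems with the iodine statement.

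- **Number analysed.** The 120 per arm was reached by adding women expected to be lost and by allowing for three arms. A detectable difference computed on all 120 treats those women as analysed, and it makes no allowance for two comparisons with control.
- **Spread.** The survey reports only a median and quartiles. Turning the interquartile range into an SD with a factor of about 1.35 assumes a normal distribution, but the quartiles lie 39.1 µg/L below and 73.8 µg/L above the median.
- **Label.** Beta is the type II error rate, so a beta of 0.90 means 10% power. The folate paragraph just before it uses the term power correctly.

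Iodine status is a main objective, and both fortificants are applied in one spray. A reader will use the stated sensitivity to judge how informative a finding of little or no iodine difference is, so the figure should describe the women likely to be analysed.

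**Working it through.** **Inputs.** From the Sample size estimates section: median 96.7, quartiles 57.6 and 170.5 µg/L; alpha 0.05; intended power 0.90; 120 women per arm; 15% attrition; two comparisons with control. Sidedness is not stated. Two-sided is inferred because 2 × (3.2415/0.5)² = 84.1, rounded up to 85, reproduces the folate number.

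**Formulas** (two means, normal approximation):
- Detectable difference = SD × (z for alpha + z for power) × √(2/n)
- Power for 35 µg/L = Φ(35/(SD × √(2/n)) − z for alpha)

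**1. Reproducing 35 µg/L.** SD = (170.5 − 57.6)/1.35 = 112.9/1.35 = 83.6. With n = 120: 83.63 × (1.960 + 1.2816) × √(2/120) = 83.63 × 3.2415 × 0.1291 = 35.0 µg/L. Taken literally, 10% power would give 83.63 × (1.960 − 1.2816) × 0.1291 = 7.3 µg/L, so 35 was plainly computed with power 0.90.

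**2. Allowing for attrition.** 120 × 0.85 = 102 (or 120/1.15 ≈ 104).
- n = 102: 83.63 × 3.2415 × 0.1400 = 38.0 µg/L. Power for 35 = Φ(2.989 − 1.960) = 85%.
- n = 104: 37.6 µg/L, power for 35 about 85%.

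**3. Splitting alpha over two comparisons** (0.025 each, z = 2.241; an illustration, since the article names no method).
- n = 120: 38.0 µg/L, power for 35 = 84%.
- n = 102: 83.63 × 3.523 × 0.1400 = 41.3 µg/L, power for 35 = Φ(2.989 − 2.241) = 77%.

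**4. Skewness.** On the log scale the quartiles are nearly symmetric: ln(96.7/57.6) = 0.52 and ln(170.5/96.7) = 0.57. The log SD is ln(170.5/57.6)/1.349 = 0.804. At n = 102 and unadjusted alpha, the detectable log difference is 0.804 × 3.2415 × 0.1400 = 0.365, a ratio of 1.44.
- Upward from the median: 96.7 × 0.44 ≈ +43 µg/L.
- Downward: 96.7 × (1 − 1/1.44) ≈ −30 µg/L.
- Power for a 35 µg/L rise (96.7 to 131.7): 78%. For a 35 µg/L fall (96.7 to 61.7): 98%.

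**5. What would restore 35 µg/L at n = 102** (normal SD, unadjusted alpha). Adjusting for baseline multiplies the SD by √(1 − ρ²). This requires 1 − ρ² = (35/37.96)² = 0.85, so ρ ≈ 0.39. Equivalently, the SD would have to be about 8% lower (35/37.96 = 0.92). With alpha 0.025, ρ would need to be about 0.53.

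**The case against.** The strongest reply is that the figure may still be attainable. The planned analysis adjusts for baseline, every woman has a baseline 24-hour urine, and the article expects 24-hour collections to do better than single samples. A baseline correlation of about 0.39, or an SD about 8% smaller, recovers 35 µg/L at 102 per arm with unadjusted alpha. This stands, and it rules out saying that 35 µg/L is achievable only if nobody drops out. But the article states neither a correlation nor a reduced SD, and it presents the 24-hour gain as additional to the 35.

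Second, 102 is not established as the number of analysed urines. The 15% sits beside a six-month folate comparison, while the main intervention urine falls on one day between weeks 4 and 24, so losses may be smaller. Against that, collections that fail the volume, duration or completeness criteria are not analysed. The 102 is therefore the protocol's own attrition rate carried over, not a known count.

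Third, a one-sided alpha of 0.05 would give 35 µg/L with 98 per arm. The folate number is reproduced only with a two-sided test, so this is an unlikely reading.

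A reader might also go further and infer that power is only about 50%, with a detectable difference near 58 µg/L. Those figures follow if a lognormal is fitted to the quartiles (raw SD about 127.5) and raw means are compared without baseline adjustment at 102 per arm. That rests on an assumed shape and on an analysis scale that the article does not fix, so it is not a fair headline.

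Nor can an all-pairs adjustment such as Tukey's be read in as the protocol's own. The article does not name its three-arm adjustment, and the iodine statement concerns two comparisons with control.

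**Conclusion.** The point holds as a modest correction. The stated 35 µg/L corresponds to 120 analysed women per arm, two-sided unadjusted alpha 0.05 and a normal-theory SD of 83.6 µg/L. On the protocol's own attrition it becomes about 38 µg/L, with power for 35 falling from 90% to 85%. If alpha is also split over the two comparisons, it becomes about 41 µg/L with 77% power. These results assume the survey spread applies and that baseline adjustment brings no gain. The beta label is wrong regardless of any assumption.

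A reader might infer that the trial is insensitive to folic acid reducing iodine delivery. The documents do not support that. On the log scale, which fits the quoted quartiles better, a fall of 35 µg/L from the median keeps about 98% power at 102 per arm with unadjusted alpha. The shortfall applies to a rise or to a raw mean difference. Iodine did not determine the sample size, so enrolment is not in question.

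**What to change.** In the Sample size estimates section, or in the statistical analysis plan before analysis:

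- Write power=0.90 (beta=0.10).
- Restate the detectable iodine difference for evaluable women, about 102 per arm, and say how that number was obtained.
- Preferably give it as a ratio on the log scale (about 1.44 at 102 per arm with unadjusted alpha), with its upward and downward equivalents at the median.
- Say whether a multiplicity adjustment applies to the two comparisons with control.
- If 35 µg/L is to be kept, state the assumed gain that supports it, either as a baseline correlation (about 0.39 under the normal SD and unadjusted alpha) or as a reduced SD from 24-hour collection.

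The cost is wording only. The quoted sensitivity becomes somewhat less favourable unless a gain is justified, and no change to enrolment or procedures follows.

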### Data management and statistical analysis

For most types of data, information will be collected using automated (tablet-based) data entry with range checks and consistency checks incorporated into the data entry software. One exception is the dietary intake data, which will be recorded first on paper forms for preliminary review before entering the consolidated food intake data into the database.

Open Data Kit (ODK) software will be used for primary data collection.^57^ The records will be submitted to a web-accessible ODK aggregate database installed in a dedicated, secure server at EPHI. All sets of up-to-date raw data will be archived in comma-separated value (CSV) format. The archived data will be the aggregated data from each record that formed the basis for editing and analysis. First, all identifiable information will be removed and individual records will be coded just by the participant identification numbers. Deidentified raw data will be retained at EPHI and transferred to UC Davis weekly for editing, generating additional data reports and archiving.

The data managers at EPHI and UC Davis will jointly prepare the data editing syntax, which will be accessible to the appropriate co-investigators, along with the raw data and any data correction forms. Raw CSV data will be exported to STATA V.17 software, and data review and editing will be performed using the same software, for which STATA syntax will be developed. For errors, mistakes or missing data identified during data review, a separate data correction form will be completed and signed by the data collector, supervisor and field coordinator.

A detailed statistical analysis plan will be completed and posted publicly before the analysis is initiated. All study personnel will remain blinded to intervention group assignment (A, B or C) until investigators have reached agreement on result interpretation. Briefly, the data analysis will consist of descriptive analyses of sociodemographic data, anthropometry, blood pressure and vitamin and mineral status at baseline, followed by group-wise comparisons of change in folate and iodine status using both intention-to-treat and per protocol analyses. All data collected from women who subsequently withdraw from the study will be retained and included in the intention-to-treat analyses. Group-wise comparisons of possible adverse metabolic effects will be completed initially just in the control group versus higher folic acid group.

Variable distributions will be described using means, prevalences and percentiles, as appropriate. Generally, intervention effects will be assessed using analysis of covariance models to estimate group mean differences for continuous outcomes controlling for baseline measurement. Models will be repeated in minimally adjusted and multivariable models to increase the precision of intervention effect estimation. A similar approach will be taken for categorical outcomes using log-binomial or modified Poisson regressions (dependent on model convergence) to estimate prevalence ratios across groups. Prespecified effect modification (eg, by baseline RBC folate concentration, markers of vitamin B_12_ status, genetic polymorphisms and selected household socioeconomic and demographic variables) will be assessed by incorporating interaction terms into the models, followed by regions of significance or stratified analyses to understand the nature of effect modification.

In addition to measuring the impact of the intervention, we will model the levels of folic acid intake necessary to achieve selected RBC folate concentrations. This will be done by using the distribution of RBC folate in the control group to characterise what distribution shift would be necessary to move nearly all (>95%) of the women above the target concentration to minimise the risk of NTDs. Next, the differences in final distributions between the control group and the two intervention groups will be used to interpolate what folic acid fortification level would achieve the desired distribution shift.

### Management of trial

Major decisions on scientific aspects of the trial will be the responsibility of the co-PIs and co-investigators, who will also recruit, train and supervise the other members of the study team. Day-to-day operations will be managed jointly by the field coordinator from EPHI and a postdoctoral research fellow from UC Davis. The field team will be organised into separate domains of activity, including participant screening, enrolment and anthropometry; blood collection and processing; distribution of salt and assessment of compliance; dietary assessment and 24-hour urine collections; blood collection and preliminary processing; laboratory analysis; data analysis; and administration and logistics. Study participants will be recruited over a period of 3 months, and all primary data and specimen collections should be completed within 9 months.

Senior members of the EPHI field team will be involved in different aspects of institutional and community sensitisation, as appropriate. Ministry of Health and other public sector administrators have been contacted at the regional, zonal, woreda and kebele levels to explain the research, address any concerns and facilitate project-related activities. The health facility heads in the study area have authorised data collection activities and access to local health facilities. Separate meetings are being convened with individual (political, religious and traditional) community leaders and potential study participants and their families.

All data collection and laboratory procedures will conform to written instructions compiled in a standard operating procedures manual. A separate statistical analysis plan will be prepared before initiation of the data analysis. Data entry forms will be drafted, field tested and revised accordingly. The forms will be prepared in English, translated into the local language (Oromiffa) and back-translated to English. In most cases, these forms will then be converted to a digital data entry platform, as described above.

Quality assurance procedures related to the salt production and stability are described above. The field supervisors, field coordinator and postdoctoral fellow will supervise all day-to-day data collection procedures at the field site. In the case of the salt distribution, the field coordinator will visit all study homes on at least two occasions throughout the trial, according to a predetermined schedule. The purposes of the visits will be to confirm the date of the last field worker visit and check the participants’ identification cards and labels on the salt delivered, and to review the household salt storage and use practices.

The project has two advisory committees, each with specific roles and unique composition. In particular, a Scientific Advisory Group comprising global technical experts meets periodically to review the research design and study progress. Individual members are also available, as needed, to address specific questions. A second advisory group, the Project Advisory Committee (PAC), is composed mostly of representatives of national Ethiopian agencies that will help guide the implementation of the project and facilitate coordination among the different national agencies. Members of the PAC are representatives of the following government agencies: the Nutrition Coordination Office of the Ministry of Health; the Food, Beverage, and Pharmaceutical Industry Development Institute of the Ministry of Industry; the Ministry of Trade; the Ethiopian Food and Drug Authority; the Ethiopian Standards Authority; and a member of the Ethiopian House of People’s Representatives. Through these agencies, the project will align with the Ethiopian Food and Nutrition Strategy, which is overseen by the National Food and Nutrition Program Management Steering Committee. EPHI is responsible for providing technical support and serving as chair for research, monitoring and evaluation of the national Food and Nutrition Strategy.

### Safety considerations

Concerns have been raised in the scientific literature regarding several possible adverse effects of excessive folic acid intake, and these issues need to be considered by folic acid fortification programmes. One possible concern relates to the potential ‘masking’ of the haematological effects of vitamin B_12_ deficiency by folic acid administration, thereby leading to delayed recognition of vitamin B_12_ deficiency and its related neurological consequences. Indeed, the US Institute of Medicine (IOM) established its safe upper intake level (UL) for folate based on ‘suggestive evidence that folate intake [5 mg/d] may precipitate or exacerbate neuropathy in vitamin B12-deficient individuals’.^58^ The IOM UL was set at 1 mg/day based on an uncertainty factor applied to the lowest observed adverse effects level of 5 mg/day. This uncertainty factor provides a considerable margin of safety. The European Food Safety Authority used the same information and conceptual framework,^59^ and established the same UL as the IOM. However, as later summarised by Berry,^60^ several authors have disputed these analyses, because there does not, in fact, appear to be any difference in the rate of neurological disease progression due to vitamin B_12_ deficiency in relation to the level of folic acid intake. These authors concluded that there is no justification for withholding folic acid because of the possible risk of vitamin B_12_ deficiency. Instead, vitamin B_12_ status should be assessed and managed independent of folate intake. We note that the most recent nationally representative nutrition survey in Ethiopia found a 9% prevalence of vitamin B_12_ deficiency (defined as serum vitamin B_12_<191 pg/mL) among WRA.^61^

Other potential adverse effects of folic acid that have been discussed most commonly include a possible increased cancer risk due to suppressed immune function and impaired insulin sensitivity. Other diseases, like allergy and cognitive disorders, have also been postulated, although there is very little information available on these latter issues. With regard to cancer, it is well accepted that low folate intake is an independent risk factor for several types of cancer.^62^ On the other hand, some animal studies and secondary analyses of human trials have suggested that high folic acid intakes may increase the risk of colorectal cancer.^63^ However, these latter findings are inconsistent, and most trials and retrospective studies have not identified an increased cancer risk.^63^ The results of studies of the effect of folic acid on immune function are also inconsistent, and the doses of folic acid that were assessed were considerably greater than what might be delivered by a fortification programme.

With regard to folate status and glucose metabolism, an observational study in India found that 6-year-old children of women who had both low vitamin B_12_ status and high folate status during pregnancy had lower insulin sensitivity, as measured by the HOMA-IR. The authors suggested that the combination of low maternal vitamin B_12_ status and high folate status may contribute to type 2 diabetes in India.^64^ Other investigators completed a maternal folic acid intervention trial among pregnant Nepali women and applied a similar HOMA-IR method to assess insulin sensitivity in children aged 6–8 years who were born to those women. This group of researchers likewise found greater insulin resistance among the children of vitamin B_12_-deficient mothers, but there was no relationship between either maternal folate status or folic acid supplementation during pregnancy and the children’s HOMA-IR results.^65^

As reviewed in a recent paper on the safety of folic acid fortification,^66^ several expert groups have examined the foregoing concerns regarding possible adverse effects of folic acid supplementation and fortification. These expert groups include the National Toxicology Program of the US National Institute of Environmental Health Sciences,^67^ a National Institutes of Health/FDA/USDA workshop on the metabolic and clinical effects of excess folates/folic acid,^63^ the UK Scientific Advisory Council on Nutrition,^68^ the Norwegian Scientific Committee for Food Safety^69^ and New Zealand’s Office of the Prime Minister’s Chief Science Advisor.^70^ These groups all report that there are no consistent adverse effects of folic acid, and in the few cases where such events have occurred the dose of folic acid that was consumed was considerably greater than what might be provided by a fortification programme. Given the confirmed benefits of folic acid fortification for reducing the risk of NTDs, the unanimous consensus of these groups is that the benefits of folic acid fortification outweigh any unconfirmed potential risks of adverse effects and that folic acid fortification programmes should proceed, while appropriate authorities continue to monitor for any possible adverse effects.

Based on the results of our preliminary studies of 100 women’s discretionary salt intakes in the study communities, we estimate that women in the higher folic acid fortification arm whose usual salt intakes are at the 95th percentile (ie, 10.2 g salt per day) will consume 918 µg folic acid per day from salt.^25^ Thus, the vast majority of women in the study population will consume less than the UL of 1000 µg/day; and we conclude that the proposed level of folic acid fortification should not produce any adverse effects. Nevertheless, we will monitor continuously for any adverse events, and we will assess the women’s insulin sensitivity and metabolic responses to the intervention.

